#### Secondary study parameters

An independent sample *t*-test will be used to assess the differences in scores on the PBQ, W-DEQ B, WHOL-QOL and EPDS between groups on a continuous scale. Also, a chi-square test will be conducted to compare the frequencies of moderate (scores 26–40) and severe bonding disorders (scores 40 or higher) on the PBQ, the presence of FoC by using a cut-off score on the W-DEQ B of 85 or higher to indicate FoC and the differences in the prevalence of breastfeeding between groups. Linear mixed model analyses will determine the difference between the intervention group and CAU group in scores on PBQ, W-DEQ B, WHOQOL-BREF and EPDS at inclusion and at follow-up (T0 and T1). Previous psychological treatment, educational level, parity, mode of delivery and place of birth will be entered as covariates.

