#### Breastfeeding

Women will be asked whether they had the intention to breastfeed and whether they are breastfeeding at T0 and T1 by using ‘yes’ and ‘no’ questions.

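### Secondary scales are each analysed two or three ways with none named as deciding, the breastfeeding test leaves collected baseline data unused, and the PBQ classes overlap at 40

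*Protocol article*

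**What the plan says.** All of this is in the protocol article, mainly under Secondary study parameters.

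- **t-tests.** An independent-samples t-test "will be used to assess the differences in scores on the PBQ, W-DEQ B, WHOL-QOL and EPDS between groups on a continuous scale". No time point and no baseline term are given.
- **Cut-offs.** A chi-square test is to "compare the frequencies of moderate (scores 26–40) and severe bonding disorders (scores 40 or higher) on the PBQ". The same sentence covers W-DEQ B: "the presence of FoC by using a cut-off score on the W-DEQ B of 85 or higher to indicate FoC".
- **Mixed models.** "Linear mixed model analyses will determine the difference between the intervention group and CAU group in scores on PBQ, W-DEQ B, WHOQOL-BREF and EPDS", using T0 and T1. On covariates: "Previous psychological treatment, educational level, parity, mode of delivery and place of birth will be entered as covariates".
- **Breastfeeding.** The chi-square sentence ends with "the differences in the prevalence of breastfeeding between groups". No other analysis is given for it. The Breastfeeding section says women are asked "whether they had the intention to breastfeed and whether they are breastfeeding at T0 and T1".

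The Effectiveness section has the same questionnaires completed at T0 and T1, so each of the four scales has a baseline score. The PBQ section places a score of 40 in the severe class. The Aim section attaches a directional hypothesis to every secondary outcome.

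**The concern.** Each scale carries a hypothesis, but two or three p-values will be available to answer it. The methods look at different quantities: a difference between means, a difference in the share above a threshold, and a difference that takes T0 into account. They can disagree on the same data, and the text gives no rule for that case. The protocol also states that the women and the researchers are not blinded, and these scales are self-reported, so a free choice of analysis adds to an existing weakness.

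Two further points concern what the tests use and how they classify. The t-tests and chi-square tests have no T0 term although T0 is measured, which costs precision. For breastfeeding this is the whole plan, because no mixed model or other adjusted analysis is listed. And classes defined as "moderate (scores 26–40) and severe bonding disorders (scores 40 or higher) on the PBQ" are not mutually exclusive, so the chi-square table cannot be built as written for a woman who scores 40.

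**Working it through.** **The plan's own figure.** The only sample-size figure is for the PCL-5: difference 10, SD 20, alpha 0.05, power 90.3%. Normal approximation, two-sided: n = 2 × (1.960 + 1.299)² × (20/10)² = 85 per arm. The noncentral t distribution at 86 per arm gives power 90.3%. With 20% loss, 86/0.8 = 107.5, so 108. The figure reproduces and is untouched by this point. The 86 evaluable women per arm are used below.

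**Count of analyses.** PBQ 3, W-DEQ B 3, WHOQOL-BREF 2, EPDS 2, breastfeeding 1: 11 in all. If the four WHOQOL-BREF domains were tested separately, which the article does not state, there would be 17.

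**Error per scale.** If the analyses were independent, the chance of at least one p<0.05 under the null would be 1 − 0.95² = 9.75% for two and 1 − 0.95³ = 14.3% for three. They are not independent, so they were simulated: 86 per arm, 20,000 runs, T1 t-test, change-score test, and a T1 cut-off exceeded by 25%. The change-score test stands in for the mixed model's time-by-group term.

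| Assumed T0–T1 correlation | Two analyses | Three analyses |
|---|---|---|
| 0.3 | 8.8% | 11.8% |
| 0.5 | 9.0% | 12.1% |
| 0.7 | 9.6% | 12.5% |

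Each single test stays close to 5%. With an assumed true effect of 0.4 SD, the t-test and the change-score test disagree on significance in about 25–29% of simulated trials.

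**Precision.** Relative to a T1-only t-test (variance 1), a T0-adjusted analysis has variance 1 − ρ² and a change-score analysis 2(1 − ρ). Power is for an illustrative 0.4 SD difference at 86 per arm; the T1-only t-test has 74.6%.

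| ρ (assumed) | Adjusted: variance | Adjusted: power | Change: variance | Change: power |
|---|---|---|---|---|
| 0.3 | 0.91 | 78.5% | 1.40 | 60.1% |
| 0.5 | 0.75 | 85.7% | 1.00 | 74.6% |
| 0.7 | 0.51 | 95.7% | 0.60 | 92.3% |

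The last two columns show that including T0 in a mixed model does not by itself secure the gain. If the tested term is a time-by-group interaction with free baseline means, it behaves like a change score. The secondary section does not say which term is tested.

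**Breastfeeding.** The documents give no rates, so all inputs are assumptions: the share feeding at T0, the share of these still feeding at T1 in each arm, and no late starters. The all-women proportions are the products of these shares. Two-proportion power, two-sided 0.05:

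| Feeding at T0 | Still feeding at T1 | All women, 86/arm | Feeding at T0 only |
|---|---|---|---|
| 75% | 70% vs 85% | 52.5% vs 63.75%: 32% | 64/arm: 53% |
| 90% | 70% vs 85% | 63% vs 76.5%: 49% | 77/arm: 61% |
| 75% | 80% vs 90% | 60% vs 67.5%: 17% | 64/arm: 35% |

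The right-hand column is power in a subset, used as a stand-in for an analysis that conditions on T0 status. It is not the power of a regression in all women.

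**PBQ.** Moderate runs from 26 to 40 inclusive and severe starts at 40, so the two share the value 40. The PBQ section assigns 40 to severe. The disjoint classes are therefore 26–39 and 40 or higher.

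**The case against.** The ranking of secondary analyses and any multiplicity correction are commonly left to a SAP, which is not shown. That is fair as regards a correction across outcomes, and its absence is not counted here. It does not cover the rest: the article itself states several methods for the same scale, and states the overlapping classes.

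A reader might also infer stronger claims that the documents do not support:

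- **That the unadjusted tests are biased.** They are not. Randomisation keeps them valid.
- **That T0 is ignored for the scales.** The mixed models include it for all four. The loss of precision belongs to the simple tests, and to the mixed models only if the tested term acts as a change score.
- **That the false-positive risk is 58%.** 1 − 0.95¹⁷ = 0.58 is a ceiling. It assumes independence between analyses of the same women and a separate test of each WHOQOL-BREF domain. Much of it comes from having several outcomes: eight independent tests, one per outcome or domain, already give 1 − 0.95⁸ = 0.34. The per-scale figures isolate the effect of duplicate analyses.
- **That the breastfeeding loss has a known size.** It rests on assumed rates and moves widely with them. That the chi-square test is at T1 and in all women is also an inference, by analogy with the CAPS-5 test; the article states neither.

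The PBQ overlap concerns one score value and is editorial in weight. The other section of the article already settles it.

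**Conclusion.** The point holds in a limited form. Four secondary scales have two or three stated analyses and no deciding one. That raises the chance of at least one nominally significant result on a scale with no effect from 5% to about 9% or 12%. These figures rest on the assumed T0–T1 correlation of 0.3–0.7, the assumed 25% above the cut-off, and the change score as stand-in for the mixed model. At the same correlations, a T0-adjusted analysis has 91% down to 51% of the variance of a T1-only t-test.

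Breastfeeding has a single unadjusted test although strong candidate covariates are recorded before allocation is disclosed. The direction of the gain is plain, but its size cannot be fixed from the documents. The PBQ overlap is a definite wording error.

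Only secondary outcomes are affected. The change should be made, but the primary conclusion and the sample size do not depend on it.

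**What to change.** 1. For PBQ, W-DEQ B, WHOQOL-BREF and EPDS, name one deciding analysis: the baseline-adjusted difference at T1, from ANCOVA or from a mixed model with a common baseline mean for both arms. State that the t-tests are supportive and the cut-off tables descriptive. They need not be deleted.
2. Analyse T1 breastfeeding by regression adjusted for T0 status and intention to breastfeed, and state the time point and population.
3. Change the moderate PBQ class to 26–39, in line with the PBQ section.

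A Holm correction across the secondary outcomes is an option, not a necessary part of the change.

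Cost: no new data, visits or participants. The article says recruitment has started and that modifications go to the ethics committee, so a small protocol amendment is needed. Fewer nominally significant secondary results should be expected.

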#### Postpartum Bonding Questionnaire (PBQ)

Mother to infant bonding is assessed by using the PBQ [46]. It consists of 25 statements, each followed by a 6-point Likert scale ranging from ‘Always’ (0) to ‘Never’ (5) with a range of 0–125 with higher scores reflecting a problematic mother-to-infant bond. Good validity and reliability of the Dutch version of the PBQ have been found [58]. To analyse the effects of PTSD symptom severity on the PBQ, only the total score will be used since later validation studies have not been able to replicate its factor structure. A score of 26 or higher is suggesting for some kind of bonding disorder, whereas a score of 40 or higher indicates severe bonding disorders [59].

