### Sample size calculation

Based on a mean difference between two treatment arms of at least 10 points on the PCL-5 scale and a standard deviation of 20, 86 patients are needed for this study to be included in each arm. Considering up to 20% loss to follow-up, 108 patients need to be included per treatment arm. We consider this sample size calculation to be conservative; the mean and difference estimates used were based on previous studies with PCL-5 score as the primary endpoint [61, 62]. The calculation was performed in PASS v11 [63] using an alpha of 0.05 and a power of 90.3%.

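### The chi-square on a closed 'moderate' PBQ band (26–40) does not move consistently with benefit and overlaps the severe class at 40; testing 26 or higher and 40 or higher avoids both

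*Protocol article*

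**What the plan says.** The PBQ entry under Instruments describes a total score "with a range of 0–125 with higher scores reflecting a problematic mother-to-infant bond". It then gives two nested cut-offs: "A score of 26 or higher is suggesting for some kind of bonding disorder, whereas a score of 40 or higher indicates severe bonding disorders". The word moderate does not appear there.

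Under Secondary study parameters, PBQ scores are first compared by an independent t-test, which "will be used to assess the differences in scores on the PBQ, W-DEQ B, WHOL-QOL and EPDS between groups on a continuous scale". The categorical comparison follows, as a chi-square test to "compare the frequencies of moderate (scores 26–40) and severe bonding disorders (scores 40 or higher) on the PBQ". The same paragraph adds a longitudinal analysis: "Linear mixed model analyses will determine the difference between the intervention group and CAU group in scores on PBQ" and the other scales at T0 and T1.

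The proportion scoring 26 or higher, which is the Instruments section's cut-off for any bonding disorder, is not listed as a comparison. The article does not say whether the chi-square is one table of three classes by two arms or a separate test for each class.

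**The concern.** The frequency of a middle class is a poor outcome to test between arms. It loses cases at its lower edge when women improve out of disorder, and gains cases at its upper edge when women improve out of the severe range. A move from 45 to 35 is an improvement, yet it counts as a new moderate case and offsets a woman who falls below 26. A result of no difference, or of more moderate cases on EMDR, is therefore hard to interpret.

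Separately, a score of exactly 40 belongs to both classes as written, so the classes are not mutually exclusive and a table built from them is not well defined for that score.

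Bonding is a stated secondary objective with a directional hypothesis. What is at stake is a reported bonding result that could be misread, for instance as severe disorder down but moderate disorder up.

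**Working it through.** **Inputs from the documents.** Cut-offs 26 and 40 (PBQ instrument entry); classes 26–40 and 40 or higher (Secondary study parameters); 86 evaluable women per arm (Sample size calculation). No PBQ mean, SD or category rate is given, so all PBQ distributions below are assumptions.

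**The plan's own figure.** The sample size rests on a "mean difference between two treatment arms of at least 10 points on the PCL-5 scale and a standard deviation of 20, 86 patients" per arm. The standardised difference is 10/20 = 0.5. With two-sided alpha 0.05 and 86 per arm, power is 90.3% by the noncentral t, and 86/0.80 = 107.5 rounds up to 108. The stated figures reproduce. They concern the PCL-5, and only the 86 per arm is carried forward.

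**Step 1: why the band is not monotone.** With the band cut cleanly at 26–39:

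P(band) = P(26 or higher) − P(40 or higher)

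so the reduction in the band equals the reduction at 26 minus the reduction at 40. If treatment lowers both proportions equally, the band does not change. If it lowers the severe proportion more, the band rises. Removing the overlap at 40 does not alter this.

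**Step 2: worked counts.** Assume 86 per arm and control counts (none/moderate/severe) of 56/15/15. For each two-class comparison, the Pearson chi-square without continuity correction is d² / [p(1 − p)(2/86)], where d is the difference in proportions and p the pooled proportion.

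- (A) Ten women move from severe to moderate only: EMDR 56/25/5.
- (B) Ten move from severe to moderate and ten from moderate to none: EMDR 66/15/5.

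Example, severe 15 v 5: p = 20/172 = 0.1163, d = 10/86 = 0.1163, chi-square = 5.66, p-value 0.017.

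| Comparison (control v EMDR) | A | B |
|---|---|---|
| Moderate band | 15 v 25, p = 0.071 | 15 v 15, p = 1.00 |
| Severe, 40 or higher | 15 v 5, p = 0.017 | 15 v 5, p = 0.017 |
| 26 or higher | 30 v 30, p = 1.00 | 30 v 20, p = 0.093 |
| One unordered 3×2 table | p = 0.024 | p = 0.055 |

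In A, pure improvement looks like more moderate disorder. In B, improvement at both steps gives no difference in the band.

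**Step 3: power under assumed scores.** 20,000 simulated trials per scenario, 86 per arm, two-sided 5%, whole-number scores limited to 0–125, band taken as 26–39. Repeat runs differ by about one percentage point.

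| Shape, control mean, SD, EMDR reduction | Band | 26 or higher |
|---|---|---|
| Normal, 20, 15, 5 | 20% | 39% |
| Normal, 30, 15, 5 | 8% | 43% |
| Normal, 35, 15, 7.5 | 6% | 71% |
| Gamma, 20, 15, 5 | 22% | 32% |
| Gamma, 30, 15, 5 | 20% | 53% |
| Gamma, 35, 15, 7.5 | 21% | 87% |
| Normal, 15, 12, 5 | 34% | 41% |
| Gamma, 15, 12, 5 | 22% | 25% |

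The second row can be checked by hand with cut points 25.5 and 39.5. Control: Φ(4.5/15) = 61.8% at 26 or higher, less 1 − Φ(9.5/15) = 26.3% at 40 or higher, leaves 35.5% in the band. EMDR (mean 25): 48.7% − 16.7% = 32.0%. A fall of 13.1 points at 26 and 9.6 points at 40 leaves only 3.5 points in the band. In that row the band has numerically more cases on EMDR in about 28% of trials, and in the third row in about 40%.

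**Step 4: the overlap at 40.** Under normal scores from mean 10, SD 10 to mean 25, SD 15, the expected number scoring exactly 40 among 172 women is about 0.1 to 3. The definition is faulty, but the numerical effect is small.

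**The case against.** A reader might infer that the two sections contradict each other. They do not: a moderate class, meaning disorder that is not severe, follows from the two cut-offs. Only the treatment of exactly 40 is inconsistent.

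A reader might also infer that a real benefit would be cancelled. The documents do not support that either. The same sentence compares severe cases, where a move from 45 to 35 shows, and the score is also analysed by t-test and mixed model. The categorical test is introduced as an addition to these. In the three normal scenarios with SD 15, in table order, power is about 20%, 35% and 69% for the severe comparison and 57%, 59% and 90% for the t-test. If the chi-square is read as one unordered 3×2 table, its power is 31%, 39% and 74%; across all eight scenarios it loses at most about 12 points against 26 or higher. Its remaining weakness is that it ignores the order of the classes and gives no direction.

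Nor is a false finding of harm likely. The 28% and 40% count any numerical excess. A significant excess of moderate cases on EMDR occurs in under 2% of trials, below the 2.5% expected by chance with no effect.

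The starkest scenarios assume that about 62% and 74% of untreated women are above the cut-off of 26. Eligibility rests on a traumatic birth experience, not on bonding problems, so lower scores are quite possible, and there the loss is small.

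Finally, 26 or higher does not register a severe-to-moderate move (30 v 30 in A). That is true, and it is why the remedy needs both cumulative proportions.

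These points limit the size of the concern. They do not make the band frequency a sound outcome to test by itself.

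**Conclusion.** The point stands in a limited form. If the moderate band is tested on its own, the comparison can be flat or numerically reversed when bonding improves, and the classes overlap at 40. The band had less power than 26 or higher in all eight assumed scenarios, from a trivial loss with low scores to a very large one with high scores. Which of these applies cannot be settled from the documents, because they give no PBQ distribution. The non-monotone behaviour and the overlap need no such assumption.

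The consequence is confined to one supplementary categorical comparison of one secondary outcome. This is a minor point and a cheap improvement.

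**What to change.** In Secondary study parameters, replace the comparison of moderate and severe frequencies with two cumulative proportions taken from the instrument entry: PBQ 26 or higher (any bonding disorder) and PBQ 40 or higher (severe). Show the 26–39 band by arm descriptively, without a test.

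Improvement can then only lower each tested proportion or leave it unchanged, apart from sampling variation. The pair covers both steps of improvement, and a score of 40 is always severe. Stating two separate two-by-two comparisons also settles how the chi-square is to be run.

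The cost is one sentence of analysis wording, with no new data and no extra participants. The only thing given up is a separate p-value for the moderate band.

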## Methods and design

### Aim

The main purpose of the study is to determine the safety and effectiveness of ‘early intervention EMDR’ in preventing PTSD or reducing symptoms of PTSD at 9 weeks postpartum in women with a traumatic birth experience, and to compare these results with care as usual (CAU) in women who experienced their delivery as a traumatic event. Safety is defined as the absence of all of the following adverse events: increased suicidal ideation, serious self-injurious behaviour or crisis contacts for any of the aforementioned reasons [37]. It is hypothesized that early intervention EMDR therapy is safe and that women who receive early intervention EMDR will report significantly less PTSD (symptoms) 9 weeks after the delivery compared to women who receive no treatment. Furthermore, our secondary objectives are to determine the effects of early intervention EMDR therapy on FoC, QoL, mother-infant bonding (MIB), breastfeeding and depression. It is hypothesized that early intervention EMDR will significantly reduce FoC, improve QoL and MIB, increase the success of breastfeeding and prevent or reduce depressive symptoms as compared to CAU.

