### Patients

#### Inclusion criteria

Women less than 14 days postpartum who report a traumatic birth experience will be asked to participate in this study. Medical deliveries as well as women who had a delivery supervised by a primary care midwife from community midwifery practices in Amsterdam will be included. Furthermore, they must understand the Dutch language.

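### The hypothesis is breastfeeding success and intention is recorded, but the planned test compares breastfeeding prevalence without using intention: a valid comparison, but an attenuated one

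*Protocol article*

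**What the plan says.** Under Aim, the hypothesis for this outcome is that early EMDR will "increase the success of breastfeeding and prevent or reduce depressive symptoms as compared to CAU". The article does not define success.

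Under Instruments, Breastfeeding, the data are yes/no answers: "Women will be asked whether they had the intention to breastfeed and whether they are breastfeeding at T0 and T1".

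Under Secondary study parameters, one sentence covers the analysis. It opens with "a chi-square test will be conducted to compare the frequencies of moderate" and severe bonding disorders, goes on to fear of childbirth above a cut-off, and ends with "the differences in the prevalence of breastfeeding between groups". No denominator, stratum or covariate based on intention is named. Breastfeeding is not among the mixed-model outcomes, and the covariate list for those models does not contain intention: "Previous psychological treatment, educational level, parity, mode of delivery and place of birth will be entered as covariates".

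Eligibility does not depend on feeding plans: "Women less than 14 days postpartum who report a traumatic birth experience will be asked to participate in this study". The exclusion criteria do not mention them either.

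**The concern.** Prevalence gives the same value to two different women: one who wanted to breastfeed and is not doing so at 9 weeks, and one who never planned to. Only the first bears on success in any ordinary sense of the word. The intention item is what separates them, yet the stated analysis does not use it.

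Women in the second group have little or no room to respond to treatment on this outcome. They are expected in both arms alike, so they pull the arm difference toward zero. The risk is that a real effect among women who wanted to breastfeed is missed, and that a null result on prevalence is then reported as no effect on success.

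**Working it through.** **Inputs from the protocol article.** The sample size section states that "86 patients are needed for this study to be included in each arm", from a "mean difference between two treatment arms of at least 10 points on the PCL-5 scale and a standard deviation of 20". That figure reproduces: the two-sided noncentral t gives 90.3% power at 86 per arm, and 86 / 0.8 = 107.5, rounded up to 108. It was derived for the PCL-5, not for breastfeeding. It is used here only as the number of evaluable women per arm.

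**Assumptions, because the article gives no figures.**
- q, the share who intended to breastfeed: 0.70 to 0.95.
- Breastfeeding at T1 among intenders: 55% (CAU) versus 75% (EMDR).
- Women who did not intend to breastfeed do not breastfeed at T1.

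**Attenuation.** If p is the rate among intenders, the rate in all women is q × p. The difference in all women is therefore q × (p2 − p1). At q = 0.80 this gives 0.80 × 55% = 44% versus 0.80 × 75% = 60%, so 16 points instead of 20.

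**Power.** Normal approximation to the two-sided 5% chi-square test, with n = 86 per arm for all women and 86q per arm for intenders:

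power = Φ[(d − 1.96 × SE0) / SE1]

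where SE0 = √(2 p̄(1 − p̄)/n), p̄ is the mean of the two rates, and SE1 = √((p1(1 − p1) + p2(1 − p2))/n).

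At q = 0.80:
- All women: d = 0.16, SE0 = 0.0762, SE1 = 0.0752. (0.16 − 0.1493)/0.0752 = 0.142, power 0.556.
- Intenders (68.8 per arm): d = 0.20, SE0 = 0.0813, SE1 = 0.0795. (0.20 − 0.1594)/0.0795 = 0.511, power 0.695.

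| q | All women: rates | Difference (points) | Power, all women | Power, intenders only |
|---|---|---|---|---|
| 0.95 | 52.3% vs 71.3% | 19 | 73% | 77% |
| 0.90 | 49.5% vs 67.5% | 18 | 67% | 75% |
| 0.80 | 44% vs 60% | 16 | 56% | 70% |
| 0.70 | 38.5% vs 52.5% | 14 | 45% | 64% |

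**Does the direction depend on the assumed rates?** Not under the third assumption. The squared signal-to-noise ratio in all women is n q (p2 − p1)² / [p1(1 − q p1) + p2(1 − q p2)]. In intenders only, it is n q (p2 − p1)² / [p1(1 − p1) + p2(1 − p2)]. The numerators are equal, and for q below 1 each term 1 − qp exceeds 1 − p, so the intenders-only analysis has the larger ratio despite its smaller denominator. Other assumed rates at q = 0.80 agree: 60% versus 80% gives 56% versus 73%; 50% versus 70% gives 56% versus 67%; 70% versus 85% gives 37% versus 56%.

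**The case against.** The case for leaving the plan alone has several parts.

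- **Denominator.** The analysis sentence does not say all women, and an analysis plan that is not shown might use intention. It is true that all women is a plain reading and not a stated phrase. But the article does name the measure and the test, and that measure is not the quantity in its hypothesis. The point rests on what is stated.
- **Meaning of success.** The word is used once, undefined; elsewhere the outcome is simply breastfeeding. All-women prevalence answers a legitimate question in the full randomized population. This stands, and it is why prevalence should be kept as a supportive result.
- **Scoring.** A reader might infer that the plan scores women who never intended to breastfeed as failures. It does not: it tabulates yes and no, and attaches no such label.
- **Bias.** A reader might infer that an imbalance in intention distorts the comparison. Randomization balances intention in expectation, and the Type I error rate is preserved. The chance imbalance has a standard deviation of √(2q(1 − q)/86), which is 4.6 points at q = 0.90 and 7.0 at q = 0.70, but it is already part of the test's sampling error and is no separate defect.
- **Size.** Every power figure rests on assumed rates. If nearly all women intended to breastfeed, little is lost. This stands.
- **Remaining dilution.** Women who intended to breastfeed but stopped before T0 stay in an intenders-only denominator, and intention is recalled about two weeks after birth. Both stand as limits of the remedy.

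**Conclusion.** The concern holds as a mismatch between hypothesis and test that costs power. It does not hold as a claim of bias. The planned chi-square test is a valid comparison of prevalence between arms. As a test of the hypothesis under Aim, with success judged against the woman's own intention, it is attenuated by the factor q.

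Under the assumed 55% versus 75% and 86 evaluable women per arm, the loss of power is about 4 points at q = 0.95 (73% versus 77%), 8 at q = 0.90 (67% versus 75%) and 14 at q = 0.80 (56% versus 70%). The direction follows from the algebra if non-intenders do not breastfeed; the size cannot be fixed from the article. The trial was not sized for this outcome. It is one of several secondary outcomes, and the CAPS-5 and PCL-5 analyses are unaffected.

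**What to change.** Under Secondary study parameters, make the main breastfeeding comparison the proportion breastfeeding at T1 among women who reported at T0 that they had intended to breastfeed. Stratifying by T0 intention or adjusting for it would serve the same purpose. Report all-women prevalence as supportive.

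Use only the T0 answer. According to Procedures and interventions, women learn their allocation after completing T0, so that answer cannot be influenced by knowledge of the arm; an answer given at T1 could be.

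Adjusting also for breastfeeding status at T0, which is already collected, would reduce the dilution left by intenders who had stopped before T0.

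The cost is a sentence or two and no new data. The downsides are a somewhat smaller denominator, reliance on intention recalled about two weeks postpartum, and some dilution that remains. The choice should be fixed before outcome data are examined by arm, so that the denominator is not chosen after the result is known.
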